#### Control arm

Participants in the control arm receive usual care. As in the intervention clinics, providers in the control clinics have had prior training in the use of the mhGAP-IG. Usual care for perinatal depression in these facilities thus consists of the basic specifications of the mhGAP-IG for treating depression, and these include psychoeducation, reactivation of the social network, and addressing current psychosocial stressors. Providers decide on the number of sessions even though, if implemented according to the guide, patients with depression are expected to be seen a number of times. In this arm, there are no structured sessions of behavior activation and problem-solving treatment, no structured parenting skills training, and no engagement of a “neighborhood mother” in the provision of care to the adolescent.

### Outcome evaluation and instruments

Outcome assessments are conducted in participants’ homes or at any other place of their preference. Outcome assessors have no involvement in the delivery of the intervention and conduct the assessment blind to the participant’s study arm. Assessments of participants are being conducted at baseline (within 72 h following enrollment) and at the 3-month and 6-month postnatal periods (Table 1). Details of childbirth are obtained from the facility where delivery takes place, from the mother, and by direct measurement of the baby soon after childbirth following notification of our team by the maternal care providers.

The primary outcomes, determined at 6 months postnatal, are 1) the difference in the level of depressive symptoms as assessed with the EPDS [22] between participants in the intervention and care as usual groups; and 2): level of parenting skills as measured by the total and subscale scores on the HOME-IT.

Assessments of secondary outcomes, to be conducted at 3 or 6 months (see Table 1), consist of the following: depression remission rates (EPDS score < 6); level of disability as assessed using the WHO Disability Assessment Scale [23]; maternal attitude and adjustment to pregnancy and motherhood as measured with the Maternal Adjustment and Maternal Attitude scale (MAMAS) [24]; quality of life using the short form of the WHO Quality of Life scale, WHOQoL-BREF; and the extent of mother–infant interactions assessed using the Postnatal Bonding Questionnaire (PBQ) [18]. The family planning and new pregnancy questionnaire (designed by the investigators) will assess what measures, if any, the adolescents have taken to prevent getting pregnant soon after the index childbirth. The Perinatal Infant Care Social Support scale (PICSS) [19] will rate the availability of social support for the adolescents as they navigate the challenge of motherhood. Assessments of the infants will include weight, height, and head circumference at birth and at 3 and 6 months of age, nutrition (history of breastfeeding), vaccinations received, and the child’s social, cognitive, and physical developmental milestones.

Study instruments have been culturally adapted using standard procedures [25, 26], including translation (into the study language, Yoruba) and back-translation of the items by a panel of bilingual experts. Even though one of the primary outcome measures, the EPDS, has been used extensively by us and others in this setting [27], we conducted a test–retest reliability of the tool among adolescent mothers. The tool was administered to 25 respondents attending for antenatal care by one set of five interviews and was re-administered to the same respondents in their homes by another set of home assessors 2–3 days after (intraclass correlation: 0.50 (95% confidence interval: −0.124 to 0.777); *p* < 0.05).

Also, with regard to the assessment of parenting skills, an inter-rater reliability exercise on the HOME-IT was conducted following training and found to be good to excellent for all of the domains. Among the five outcome assessors, independently rating 18 video-recorded HOME-IT assessments, the intra-class reliability coefficients for the domains of the tool were: Responsivity 0.89; Acceptance 0.64; Organization 0.94; Learning Materials 0.98; Involvement 0.90; Variety 0.95; and for the Total score 0.95.

### Blinding and protection against sources of bias

The following steps are being undertaken to reduce the risk of bias in this trial. First, allocation was performed by a statistician with no other involvement in the study. Second, it is recognized that allocation concealment and selection bias can be a problem in cluster randomized trials when not all participants are consented and recruited prior to the allocation of clusters. Consecutive attendees at the randomized primary maternal care clinic (MCC) are being invited to participate. Study invitees are not informed of their allocation until after establishing eligibility and providing consent to participate. Consent rates in terms of both proportion and disease severity of eligible patients in both arms of the trial are being monitored. Third, the study is designed to ensure that the risk of contamination between arms is low as patients are unlikely to move from a control to an intervention clinic due to their geographical spread and because there has been no publicity regarding the availability of the intervention in other clinics. Fourth, even though blinding of participants is clearly not possible given the nature of the intervention, however, outcome assessors are not involved in delivering the intervention and are rotated between trial participants to collect data. Fifth, our primary outcomes are the severity of depression symptoms and level of parenting skills at 6 months postnatal. We are collecting the outcome data from every participant not known to have died at the time of follow-up and who has not withdrawn consent or otherwise become unavailable, regardless of compliance with allocated treatment. Sixth, we anticipate some non-collection of primary outcome data, and while the primary intention-to-treat analyses will be without imputation of missing data, sensitivity analyses will investigate various assumptions about the missing data.

### Data collection and quality control

Data collection and capture are regulated by specific steps described in a Data Management Protocol designed to ensure data integrity and quality. Quality control of field work is implemented by research supervisors, and this includes random checks on the quality of interviews (conducted by physically observing at least 10% of the interviews conducted by a research assistant). Supervisors also work with the Data Manager to check that research assistants have correctly captured the study data.

Individual data are gathered and stored electronically. Participants consenting into the trials are informed of this and receive an ID when entering the study. Questionnaire data are collected using tablets that have been programmed to capture information directly from respondents. This will ensure accuracy and security of data collection.

### Data protection

All data are being kept anonymously, using codes to identify individuals. Data are downloaded from the tablets to a server located in the central office where they will be cleaned and stored. These datasets do not contain the allocation status of the participants, which is being kept as a separate file and only for the trial statistician. Access to the datasets is possible for members of the research team through password-protected entry.

#### Process evaluation

We are conducting a comprehensive process evaluation to assess the barriers and facilitators of scaling up the intervention. The component of the project is informed by the CFIR [28], a state-of-the-art approach for exploring implementation issues. Guided by this framework, we will explore factors such as: intervention characteristics and the process of delivering the intervention (e.g. how engaging the intervention components are to providers and users); outer setting (e.g. current standard of care, workload); inner setting (e.g. organizational structure of the facilities and acceptability of the new intervention approach to both providers and patients); characteristics of key individuals (e.g. provider attitude, patients’ compliance and adherence to treatment, etc.); and process of service delivery (e.g. fidelity to guideline specifications, supervision frequency and content, etc.). We will explore these factors with providers (*N* = 15), adolescents who recover from depression (*N* = 10), and those who do not recover (*N* = 10) 6 months after childbirth.

Monitoring of adherence to trial protocol specifications is being conducted by the Trial Manager. This follows a structured format consisting of qualitative interviews and quantitative assessments. Detailed assessment of fidelity in the delivery of the intervention specifications is being conducted. This involves the live observation and rating of 20 randomly selected therapy sessions by different providers. For this purpose, we are using the 18-item Enhancing Assessment of Common Therapeutic factors (ENACT) tool [29] to evaluate the extent to which providers are applying the skills acquired to conduct focused psychological assessment of and intervention for the adolescents. ENACT is a tool that has been developed to provide reliable and valid assessment of therapist competence in a variety of cultural and service settings. This is being done by research supervisors, appropriately trained for the purpose, sitting in during clinical encounters between maternal care providers and the depressed pregnant adolescents.

### Sample size determination for the RCT

The primary outcome considered in calculating the sample size is the level of depressive symptoms as assessed with the EPDS total score at 6 months postpartum. Based on the results of our recently concluded cluster randomized controlled trial of interventions for perinatal depression in primary care in Nigeria (EXPONATE) [15] showing a standard deviation (SD) for the EPDS score of 4.5, we estimate that a mean difference of 2.0 in the EPDS score between the two arms at 6-month postnatal follow-up will represent a clinically significant difference in depression symptoms, giving a target effect size of 0.44. About 6 months into recruitment to the current trial, there was an imbalance in the ratio of participants recruited to the trial of about 1.5 in favor of the intervention arm. An uninflated sample size of 102 in the intervention arm and 68 in the control arm will be required to provide a power of 80% at an α level of 0.05. Based on prior experience, we expect to recruit seven adolescent participants per cluster over 18 months. To take account of the cluster design, we inflate the estimated cluster size by 1 + [(*k* – 1) × ICC)], where *k* is the cluster size for analysis and ICC is the intracluster correlation coefficient. In previous use of the EPDS, we obtained an estimate of 0.03 for the ICC. Using the resulting design effect of 1.18, the estimated inflated sample size is 200 (170 × 1.18). Taking account of a projected attrition not exceeding 15% at 6 months postnatal and a resulting sample size of 230, we plan to recruit from 30 clusters.

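### Thirty clinics at seven women each give 210, not the stated 230; at 15% attrition the stated clinics and yield give about 76% to 78% power instead of 80%

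*Protocol article*

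**What the plan says.** All the figures are in the protocol article, under Sample size determination for the RCT. The calculation uses EXPONATE, the investigators' previous cluster trial, "showing a standard deviation (SD) for the EPDS score of 4.5", and targets "a mean difference of 2.0 in the EPDS score between the two arms at 6-month postnatal follow-up", "giving a target effect size of 0.44". It allows for "an imbalance in the ratio of participants recruited to the trial of about 1.5 in favor of the intervention arm". Before any inflation it arrives at 170 women, 102 intervention and 68 control, a number said to "provide a power of 80% at an α level of 0.05".

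For clustering, the section says "we expect to recruit seven adolescent participants per cluster over 18 months" and takes an intracluster correlation (ICC) of 0.03. The resulting design effect of 1.18 raises 170 to 200. The last step allows for "a projected attrition not exceeding 15% at 6 months postnatal and a resulting sample size of 230, we plan to recruit from 30 clusters".

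The sections Schedule of trial recruitment and participation and Trial status both give enrolment as 15 May 2018 to 15 November 2019, which is 18 months.

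**The concern.** The section fixes three quantities that should be linked by one multiplication: women per clinic, number of clinics and total recruited. They are not. The yield of seven is tied to 18 months, and the enrolment window is exactly 18 months, so a longer recruitment period does not explain the gap.

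At stake is the power claimed for the EPDS comparison, which is the outcome the trial is sized on. The Abstract presents the trial as fully powered, and readers will use the 80% figure to judge a result that does not reach significance. If the clinic count and yield are the real plan, that figure is a little too favourable. If 230 is the real plan, the stated yield is too low.

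**Working it through.** **Inputs, all from the sample size section:** SD 4.5; difference 2.0; effect size 0.44 as rounded there (2.0/4.5 = 0.444); ratio 1.5 intervention to control; power 80%; α 0.05; seven recruits per cluster; ICC 0.03; attrition up to 15%; 30 clusters. The section does not say whether α is one- or two-sided. Two-sided reproduces its figures. One-sided would need only 53 controls (effect size 2.0/4.5), so two-sided is used below.

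**Step 1: reproduce the plan's chain.**
- Controls = (1 + 1/1.5) × [(1.96 + 0.8416)/0.44]² = 67.6, i.e. 68. Intervention = 1.5 × 68 = 102. Total 170, as stated.
- Design effect = 1 + (7 − 1) × 0.03 = 1.18, and 170 × 1.18 = 200.6, given as 200.
- 200 × 1.15 = 230, as stated.

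The chain 170, 200, 230 reproduces.

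**Step 2: the clinic count.**
- 30 × 7 = 210, which is 20 short of 230 (20/230 = 8.7%).
- 230/7 = 32.9, i.e. 33 clinics at seven each.
- 230/30 = 7.67 women per clinic.

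The clinic count does not reproduce.

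**Step 3: power if 30 clinics recruit seven each.** Analysed N = 210 × (1 − attrition). Effective N = analysed N / design effect, split 1.5:1. Power = Φ(d/√(1/n₁ + 1/n₂) − 1.96). The design effect is either held at the plan's 1.18 or recomputed with the analysed cluster size.

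At 15% attrition, analysed N = 210 × 0.85 = 178.5, or 5.95 per clinic:
- Analysed cluster size: design effect 1 + 4.95 × 0.03 = 1.1485; effective N 178.5/1.1485 = 155.4 (62.2 control, 93.2 intervention); power 77.5%.
- Design effect 1.18: effective N 178.5/1.18 = 151.3; power 76.4%.

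| Recruited | Attrition | Analysed | Power, d = 2.0/4.5 | Power, d = 0.44 |
|---|---|---|---|---|
| 210 | 15% | 178.5 | 76.4% to 77.5% | 75.5% to 76.6% |
| 210 | 10% | 189.0 | 78.7% to 79.4% | 77.9% to 78.6% |
| 210 | 5% | 199.5 | 80.8% to 81.2% | 80.0% to 80.4% |
| 230 | 15% | 195.5 | 80.0% to 80.5% | 79.2% to 79.7% |

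Each range runs from design effect 1.18 to the value at the analysed cluster size.

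**Step 4: detectable difference at 80% power, 210 recruited, 15% lost.** (1.96 + 0.8416) × 4.5 × √(1/n₁ + 1/n₂) = 2.06 (effective N 155.4) to 2.09 (effective N 151.3), against the 2.0 that the protocol calls clinically meaningful.

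**The case against.** The strongest reply is that 230 is the stated target, while seven is an expectation from experience that serves mainly to set the design effect. If the trial recruits 230, power is essentially as stated. Attrition of 15% is also a ceiling, so the shortfall needs both a yield of exactly seven and close to the maximum loss. Even then it is only a few percentage points. The Quantitative analysis section adjusts for baseline depression, which the sample size ignores. Under the normal approximation, a baseline to 6-month correlation of about 0.25 to 0.29 would restore 80% (√(1 − (2.0/2.06)²) to √(1 − (2.0/2.09)²), before rounding the differences). The same section promises emphasis on confidence intervals, which limits over-reading of a null result.

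Most of this stands, and it limits the severity. It does not remove the contradiction, because nothing in the article explains how 30 clinics at seven each give 230. The adjustment gain is only possible: the document gives no correlation and claims no such gain.

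A reader might also infer three further errors, which the document does not support:

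- **That 230 is the wrong inflation for 15% loss.** Dividing 200 by 0.85 gives 235.3, i.e. 236, whereas 230 matches 200 × 1.15. But 230 still gives about 79% to 80.5% power. The section also defines the cluster size in its formula as the one for analysis. On that definition, 170 × 1.1485/0.85 = 229.7, i.e. 230.
- **That using seven rather than the post-attrition cluster size costs power.** It does the reverse: the design effect is 1.18 instead of 1.1485, which is conservative.
- **That power should be computed from a t distribution on 28 degrees of freedom.** This would lower the figures by about 3 points, to 74.6% for 210 and 77.7% for 230 (analysed cluster size). It is not the document's method, and a small-sample correction may sit in the analysis plan, which is not shown.

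**Conclusion.** The point holds as an internal contradiction: seven per clinic, 30 clinics and 230 women cannot all be true, and the gap is 20 women. Its effect on power is conditional and modest. With 30 clinics at seven each and the full 15% attrition, power for a 2.0-point EPDS difference is about 76% to 78%, and 80% power is reached only for a difference of about 2.1. These figures rest on a two-sided 0.05 test, the normal approximation, equal cluster sizes, SD 4.5, ICC 0.03, a 1.5:1 ratio and no gain from baseline adjustment. Using the rounded effect size of 0.44 lowers them by just under one point.

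It would go too far to say that the trial as planned cannot deliver 80% power. If 230 women are recruited, it does so to within a point even at 15% loss. Severity is should-fix.

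**What to change.** Make the sample size paragraph consistent in one of two ways:

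1. Keep 230 from 30 clinics, and state the yield this assumes, about 7.7 women per clinic over the 18 months, in place of seven.
2. Keep seven per clinic in 30 clinics, and state 210 recruited, about 178 analysed at 15% attrition, and power of about 76% to 78% for a 2.0-point difference (80% power for about 2.1).

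If baseline EPDS adjustment is relied on to recover the difference under the second option, state the assumed correlation.

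The cost is a rewording of one paragraph. No extra patients are needed. The drawback of the second option is a slightly less favourable power statement.

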### Data analysis

#### Qualitative analysis

To explore factors relating to the barriers and facilitators at various stages of project execution, qualitative interviews will be transcribed. Interviews will be conducted in Yoruba and will be translated into English, following which back-translation checks will be applied. The data generated will be analyzed using thematic analysis with the assistance of a qualitative software package, MAXQDA. The exploration of the findings will utilize the realist approach to address the question of “what works for whom and in what circumstance” [30, 31].

#### Quantitative analysis

The analysis and presentation of the trial will be in accordance with CONSORT guidelines [32], with the primary comparative analyses being conducted on an intention-to-treat basis and due emphasis placed on confidence intervals for the between-arm comparisons. A full analysis plan will be developed prior to completion of data collection and discussed and agreed with the TSC.

We will use descriptive statistics to assess the balance between the trial arms at baseline for both MCC and individual participant characteristics. In order to take appropriate account of the hierarchical nature of the data, we will use multivariate mixed-effects regression models (logistic or linear dependent on outcome type) to estimate recovery from depression at 6 months for the intervention group versus the control arm, adjusting for baseline depression and randomization variables. In a secondary analysis, we will further adjust for any variables that were imbalanced between trial arms at baseline. We will analyze continuous outcomes (EPDS and GAD-7) over the 6-month postnatal follow-up period using repeated-measures analysis by including follow-up occasion as a random effect in the regression model. The primary outcome will first be analyzed by intention to treat without imputation. However, we will conduct sensitivity analyses to assess the potential effect of missing data using multiple imputation methods. No interim analysis is planned except when required to explore any undesired effect that may arise during the course of the trial and such analysis is deemed necessary and approved by the TSC.

We will use descriptive statistics to explore provider competence, as assessed by ENACT. We will evaluate the provider determinants of competence by determining the demographic predictors of scores on ENACT using regression analysis.

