#### Primary hypotheses

1. Among adolescents presenting with depression during pregnancy, the intervention package will, at 6 months postpartum, produce significant improvement in depression symptoms as assessed by the EPDS. For the purpose of this study, a mean total EPDS score difference of 2.0 between the arms will be regarded as a clinically meaningful difference in depression symptoms (see “Sample size determination for the RCT”).

2. The second primary hypothesis is that mothers receiving the study intervention will have significantly better parenting skills at 6-month postnatal follow-up compared to those receiving usual care as assessed with the HOME-IT [18, 19].

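### The repeated-measures model for EPDS treats two fixed visits as a random effect and pools them, and the text does not say which model is primary for the 6-month difference

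*Protocol article*

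**What the plan says.** Primary hypotheses: the first hypothesis is tied to one time point, namely that "the intervention package will, at 6 months postpartum, produce significant improvement in depression symptoms as assessed by the EPDS". The same paragraph takes a between-arm difference of 2.0 EPDS points as clinically meaningful. Sample size determination for the RCT powers the trial for 2.0 points at the 6-month visit.

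Outcome evaluation and instruments: the first primary outcome, determined at 6 months, is "the difference in the level of depressive symptoms as assessed with the EPDS" between the two arms. Remission (EPDS below 6) is listed as secondary. On timing: "Assessments of participants are being conducted at baseline (within 72 h following enrollment) and at the 3-month and 6-month postnatal periods". Table 1 agrees: EPDS and GAD-7 are taken at baseline, 3 months and 6 months, and not at childbirth.

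Quantitative analysis describes two models that could apply to the EPDS:

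- The first is from the class "multivariate mixed-effects regression models (logistic or linear dependent on outcome type" and serves "to estimate recovery from depression at 6 months for the intervention group versus the control arm". It is adjusted for baseline depression and the randomization variables.
- The second is for the EPDS and GAD-7 as continuous scores and spans both postnatal visits. It is described as a "repeated-measures analysis by including follow-up occasion as a random effect in the regression model". It states no arm-by-occasion term and no 6-month contrast.

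The section then says that the primary outcome is first analyzed by intention to treat without imputation, but does not say with which model. A full analysis plan is to be agreed with the steering committee before data collection ends.

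**The concern.** There are two separate defects in the sentence on repeated measures, and one ambiguity around it.

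First, a random effect treats its levels as draws from a population and estimates their variance. The 3- and 6-month visits are chosen times, the same for everyone, and there are only two of them. Two levels carry almost no information on a variance.

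Second, with a single arm term the model answers a different question from the hypothesis: the effect averaged over follow-up, not the effect at 6 months.

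The ambiguity is what gives these defects weight. The continuous EPDS score is named only under this model, while the 6-month model speaks of recovery. Two models with different estimands can therefore both be read as the analysis of a primary outcome. If that stays open, the choice could be made after the data are seen, and a pooled coefficient could be set against a 2.0-point threshold that was defined for 6 months.

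**Working it through.** **The plan's own target.** Inputs from Sample size determination for the RCT: difference 2.0, SD 4.5, ratio 1.5:1, power 80%, α 0.05 (two-sided assumed; sidedness is not stated).

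- Control n = (1 + 1/1.5) × 4.5² × (1.960 + 0.842)² / 2.0² = 66.2, rounded up to 67. The plan has 68, with 102 in the intervention arm; power with 68 and 102 is 81.0%.
- Design effect = 1 + (7 − 1) × 0.03 = 1.18; 170 × 1.18 = 200.6 (plan: 200); 200 × 1.15 = 230 (plan: 230).

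The figures reproduce, and they belong to a 6-month contrast. This point does not change them.

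**Number of occasions.** Table 1 gives two postnatal EPDS assessments, so an occasion variance has 2 − 1 = 1 degree of freedom. The 95% limits for the SD, as multiples of its estimate, are √(1/χ²) at the 0.975 and 0.025 quantiles with 1 df: 0.45 and 31.9.

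**What the arm coefficient estimates.** Let d3 and d6 be the true between-arm differences at 3 and 6 months. With complete data the two visits have equal weight, so one arm coefficient targets (d3 + d6)/2. With d6 = 2.0:

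| d3 | pooled target | minus d6 |
|---|---|---|
| 0 | (0 + 2)/2 = 1.0 | −1.0 |
| 1 | (1 + 2)/2 = 1.5 | −0.5 |
| 2 | (2 + 2)/2 = 2.0 | 0 |
| 3 | (3 + 2)/2 = 2.5 | +0.5 |
| 4 | (4 + 2)/2 = 3.0 | +1.0 |

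Conversely, d3 = 3 with d6 = 1 gives (3 + 1)/2 = 2.0, which meets the threshold while the 6-month effect is half of it.

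**Simulation check.** REML fits, 30 clusters of 7, 18 intervention and 12 control clusters, SD 4.5, ICC 0.03, complete data, 60 runs per scenario, true d6 = 2.0. The within-person correlation of 0.5 is an assumption; it affects the standard errors, not the averaging.

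| d3 | random occasion, one arm term (mean SE) | fixed occasion with arm-by-occasion, 6-month contrast (mean SE) |
|---|---|---|
| 0 | 0.90 (0.59) | 1.96 (0.67) |
| 1 | 1.58 (0.60) | 2.01 (0.68) |
| 2 | 1.90 (0.62) | 1.88 (0.69) |

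Taking the mean SE as the run-to-run SD, Monte Carlo error is about 0.6/√60 = 0.08 for the first model and 0.68/√60 = 0.09 for the second. The results therefore agree with the pooled targets 1.0, 1.5, 2.0 and with the true 2.0. Only these three scenarios were simulated; the rows for d3 = 3 and 4 in the first table are algebra.

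**Other readings of the sentence.**

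- Participant-level random slope on occasion: intercept variance, slope variance, covariance and residual variance are 4 parameters, but the covariance matrix of two visits has 3 distinct elements. The split into components is not identified.
- Loose wording for visits nested within participants within clinics: this can be fitted, but without an arm-by-occasion term it still returns one pooled arm effect.

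**The case against.** The strongest reply is that the same section already contains a 6-month comparison that allows for clustering and adjusts for baseline depression. EPDS is the only depression scale in Table 1, so the linear form of that model could well be meant for the EPDS score and the logistic form for remission. The repeated-measures model is not called primary, it also covers GAD-7, which is not a primary outcome, and its stated scope is the whole follow-up period. For a supplementary longitudinal analysis, a pooled effect is a legitimate summary.

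Most of this stands. A reader might infer that the plan has no analysis of the 6-month EPDS difference at all; the documents do not support that. What remains is that the 6-month model is described in terms of recovery, that the continuous score is named only elsewhere, and that neither model is designated primary.

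A reader might also infer that making occasion random is what removes the 6-month contrast. It is not. With complete data and one arm term, fixed occasion gives the same average, and random occasion together with a fixed arm-by-occasion term would still give the 6-month contrast. The averaging comes from the absent interaction; the random status is a separate fault. Likewise, the 4-against-3 parameter count does not make the arm effect inestimable: the marginal covariance can still be fitted, and software may only warn or require a term to be dropped.

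Finally, interaction terms and covariance structure are often left to the analysis plan, which is announced here. That excuses missing detail. It does not correct a stated instruction to treat two fixed visits as random.

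**Conclusion.** The point holds at moderate severity. As stated, the repeated-measures model is badly specified: its occasion variance is practically not estimable from two visits, and its arm coefficient is the mean of the 3- and 6-month effects. It differs from the 6-month difference by (d3 − d6)/2, that is by 1.0 point, half of the planned 2.0, if the two effects differ by 2 points. If the effects are equal there is no distortion.

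The effect patterns used are illustrations; the documents do not predict the course of the effect. Unequal effects are nonetheless plausible, because under Interventions the core sessions are antenatal while the provider calls run from after the 6-week visit to at least 6 months. The exact half-and-half weighting assumes complete data; with attrition the weights shift.

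It is not a must-fix, because the linear 6-month model may already be the intended primary analysis. If that were stated, only the poor specification of a supplementary model would remain.

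**What to change.** State in Quantitative analysis, and carry into the analysis plan before data collection ends, that the primary EPDS estimate is the between-arm difference in mean EPDS at 6 months. Then name one source for it:

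- either the linear mixed model at 6 months, with the word recovery kept for the remission outcome;
- or the repeated-measures model, with occasion as a fixed categorical effect, an arm-by-occasion term, random effects for clinic and participant, adjustment for baseline EPDS and the randomization variables, and the 6-month contrast reported.

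If the first is chosen, the repeated-measures model should still be respecified in this way and labelled supplementary. Use the same form for GAD-7 with its own baseline. Estimation by REML and the degrees-of-freedom method can be left to the analysis plan.

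The cost is wording only: no new data, no extra visit and no change to the sample size. In the simulation the 6-month contrast had a standard error of about 0.68 against about 0.60 for the pooled effect; that is the price of estimating the quantity in the hypothesis.
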